### Timing of measurements

Measurements will take place at three moments (see Figures 1 and 2):

- T0 (baseline): The patients will receive the first questionnaire from their GP or practice nurse at the time they are invited to enrol in the study. The nurse will send a postage-paid postcard with the patient number to the researchers at Maastricht University (UM). Before a patient visits the practice for the first consultation, he/she will complete the first questionnaire and an informed consent form. After each consultation, the nurse will record on a standardised form some patient characteristics like age, sex, blood pressure, cholesterol level, glucose level, height, weight and the occurrence of CVD in the family (yes or no).

- T1 (12 weeks): A second questionnaire and the pedometer will be sent to the patient's home address.

- T2 (52 weeks): The final questionnaire will be sent to the patient's home address. The nurses will be asked to record data regarding the biological parameters (cholesterol level, blood pressure, glucose, diabetes yes/no) from the most recent patient contact.

All the questionnaires, the informed consent form and a form to record the number of steps that were made are to be sent to the researchers in a postage-paid envelope after completion. Materials (questionnaires, informed consent form, recording forms for nurses, initial postcard) will carry a unique patient number.

### Data analysis

Since it is not possible to restrict our study to one primary outcome for all patients beforehand, the study will examine 6 different lifestyle changes: smoking, physical exercise, fat intake, fruit, vegetables and alcohol.

To assess the difference in primary outcomes between the arms, the arms will first be compared in terms of changes in the specific lifestyle issues, independent of the targets chosen by the intervention patients. We will use a T test for continuing variables and a χ^2 ^test for dichotomous variables.

A second analysis of primary outcomes is a multilevel regression analysis (using SPSS and MLwin), which uses adherence to the primary outcomes of lifestyle change as the dependent variables and group allocation and pre-intervention scores as independent variables. Additional independent variables will be included in the model, such as patient characteristics (age, sex, anxiety and risk of CVD). Additional regression analyses will focus on the effect at T2.

The third analysis involves constructing a simple standardised overall adherence score for the six lifestyle items, which expresses to what extent, on average, patients achieved the behaviour change goals of the national recommendations for a healthy lifestyle. The score of the intervention group will be compared with that of the control group.

Finally, the reduction in the 10-year risk of CVD will be analysed for differences between the two arms. The risk of CVD will be analysed with a multilevel regression analysis, which uses the risk at 52 weeks as the dependent variable and group allocation and pre-intervention risk as independent variables.

The secondary outcomes will also be analysed for the differences between the arms, using a T test for continuing variables and a χ^2 ^test for dichotomous variables. We also intend to use a multilevel regression analysis (using MLwin) which uses e.g. self-efficacy and attitudes at T1 as the dependent variables and group allocation and pre-intervention scores as independent variables. Additional independent variables, such as patient characteristics (age, gender, risk of CVD and socio-economic status), will also be included in the model. Additional regression analyses will focus on the effect at T2. Further analyses for subgroups of patients are also possible.

In addition, we will describe the personal targets of the patients in the intervention arm, which will be recorded by the nurses.

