### Sample size calculation and feasibility of recruitment

The study will be powered on outcomes on patient behaviour to detect an absolute 52-week, post-intervention, between-group difference of 15% (50 – 65%) in patients' self reported adherence to life-style advice on smoking, diet, alcohol and physical exercise (alpha = 0.05, power = 0.80). The figure of 50% represents the average adherence by patients with chronic diseases [13]. The power calculation for clustered data analysis assumes an intra-class correlation coefficient (ICC) of 0.04. ICC values in earlier trials among general practitioners were 0.06 [44] and 0.03 [45]. Since we expect that the nurses will perform well in terms of adhering to the working protocol, we expect a lower ICC, with a maximum of 0.04. Thus, the within-cluster variance will be almost equal to the between-cluster variance. This implies that 600 patients are needed (300 per group) at 52 weeks. It is our intention that a total of 720 patients will be recruited by the GPs or practice nurses, to compensate for an expected 15% loss to follow-up (in an earlier trial by [name], 87% of the included patients responded at the 6-month follow-up [45]). It should be possible to prospectively recruit 720 patients (36 per practice) in 6 months, as Dutch general practices each have 100–150 of these patients, who visit the practice at least once a year for regular monitoring.

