#### (4) Adapted Motivational Interviewing

In the second consultation, the nurse will apply adapted motivational interviewing to support the patient in the process of decision making about CVRM. The first step is to set the agenda for the consultation, together with the patient [36]. The patient will chose one or more key items in CVRM (smoking, physical exercise, dietary behaviour, alcohol consumption and adherence to medical treatment) in this agenda setting. After this, the nurse will assess the patient's current behaviour and motivation for change, by rating and exploring importance and confidence with respect to the chosen key items. If there is a need and sufficient motivation for change regarding one or more items, the nurse will consult with the patient to select one item as the goal for behaviour change. The nurse will inform the patient about local opportunities for individual or group support in lifestyle change that tie in with the patient's goal, if appropriate.

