### Variables and measurements

Primary outcome measures are the patients' adherence to lifestyle advice and drug treatment. The current state-of-the-art in measurement of adherence behaviour is a multi-method approach that combines feasible self-reporting and reasonably objective measures [50,13]. Specific behaviours relating to smoking, saturated fat intake, fruit and vegetable consumption, physical exercise, alcohol use and use of cardiovascular medication will be reported by patients, using validated self-reported questionnaires. For a detailed overview of the outcome measures, questionnaires and types of variables, see Tables 1 and 2. We will use pedometers at 12 weeks to measure physical exercise [51], although we recognise that this measurement may itself increase activity levels. Pedometers are reasonably accurate for walking activities [50]. Patients will be instructed to measure during 3 days in one week [52]. Body mass index will be measured as a proxy measure of healthy diet and exercise.

**Table 1 T1:** Primary outcome measures

**Outcome measure**	**Instrument **(Number of items, reference, validated yes/no)	**Analysis**
Fruit and Vegetables	8 items; [66]; Validated questionnaire	mean sum score; proportion meeting recommendations
Fat intake	35 items; [67] Validated questionnaire	mean sum score
Physical exercise	15 items; [68, 69]; validated questionnaire, modified Dutch version of the CHAMPS has not been validated.	mean; proportion meeting recommendations
Smoking	2 items; [70]; Validated questionnaire	proportion smoking
Alcohol consumption	2 items; [71]; validated questionnaire	proportion meeting recommendations
Adherence to medical treatment	5 items; (MARS) [72], not validated	mean
Cholesterol level	[6] Measured by nurse	mean score, proportion above recommendation
Blood pressure	[6] Measured by nurse	mean score, proportion above recommendation
Body Mass Index	[6] Measured by nurse	mean score, proportion above recommendation
10-year risk of CVD	based on patient's sex, age, blood pressure, cholesterol and smoking behaviour; [73];	mean score, proportion above recommendation

**Table 2 T2:** Secondary outcome measures

**Outcome measure**	**Instrument **(Number of items, reference, validated yes/no)	**Analysis**
Perception of own health behavior	1 item for each primary lifestyle outcome; question with 5-point scale	mean
Attitude towards behaviour change	1 item for each primary lifestyle outcome; question with 5-point scale	mean

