When we developed the decision aid, the IPDAS criteria for decision aids had not yet been published [65], but the decision aid does comply with most of the these criteria, namely using a systematic development process, providing information about options, presenting probabilities, disclosing conflicts of interests and using plain language. On the other hand, our decision aid does not fully meet the criteria on balancing the presentation of options, clarifying and expressing values, and guiding/coaching in deliberation and communication, although patients will be invited to deliberate about the decision making, and the motivational interviewing in our strategy is meant to help patients clarify and express values.

Cardiovascular risk is not the primary outcome of the effect evaluation because this is a pragmatic trial about the implementation of the Dutch national guideline for CVRM. To reduce the burden of data collection for the health care professionals, we will ask them to collect only the data they need for the risk estimations. There is no budget for additional data collection outside routine practice by the researchers.

Although we intended to use more objective measures for the primary outcomes of the effect evaluation, this was precluded by logistic and financial reasons. The relatively inexpensive breath carbon monoxide test is not very sensitive, and the more reliable urine cotinine marker is expensive and difficult from a logistic point of view. A biomarker for fruit and vegetables, such as carotene measurement, is expensive, and no simple biomarker for alcohol is available. The influence of information bias resulting from subjective self-reports is reduced in the data analysis, which takes the pre-intervention scores (which have the same information bias) into account. Although self-reported smoking status is known to be biased, measurement of a biological marker has various disadvantages.

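### The trial is sized on one lifestyle-adherence proportion at 52 weeks, but the analysis names no single primary outcome, and the article disagrees with itself on which outcomes are primary and at which time point

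*Protocol article*

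**What the plan says.** - **Sample size calculation and feasibility of recruitment.** The trial is powered for an "absolute 52-week, post-intervention, between-group difference of 15" percentage points, from 50% to 65%, in adherence to advice on smoking, diet, alcohol and exercise. Alpha is 0.05, power 0.80 and the ICC 0.04. The result is 600 patients at 52 weeks.
- **Abstract and Variables and measurements (text).** The primary outcomes are adherence to lifestyle advice and to drug treatment.
- **Table 1, headed as primary outcomes.** Ten rows: fruit and vegetables, fat, exercise, smoking, alcohol, drug adherence, cholesterol, blood pressure, BMI and 10-year CVD risk. The last is described as "based on patient's sex, age, blood pressure, cholesterol and smoking behaviour". Fat intake is summarised only as a mean.
- **Effect evaluation, Data analysis.** The section opens "Since it is not possible to restrict our study to one primary outcome for all patients beforehand" and lists six lifestyle items. These are compared between arms first, by t or chi-square test, and second by multilevel regression. On time point, the text on the primary regressions says only "Additional regression analyses will focus on the effect at T2". The third analysis is "constructing a simple standardised overall adherence score for the six lifestyle items", with no time point. CVD risk comes last and is explicitly analysed at 52 weeks.
- **Discussion.** "Cardiovascular risk is not the primary outcome of the effect evaluation".

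**The concern.** A sample size is a commitment about one comparison. Here the quantity that was sized is not the one the lead analysis tests, and the 52-week time point is not clearly the leading one. Nothing in the article says which result makes the trial positive. A favourable difference in any of six behaviours, at 12 or 52 weeks, could be reported as success under the plan as written. The opposite problem also arises: a real effect on overall adherence could be obscured by mixed results on single behaviours, with no stated rule for weighing them.

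The reason given for having no single primary is that no one outcome suits every patient. The third analysis answers this, because it builds one measure for every patient. A common primary was available and was ranked below the separate comparisons.

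**Working it through.** **1. The article's statements side by side**

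| Question | One place | Another place |
|---|---|---|
| How many primary outcomes? | Sample size: one adherence proportion | Data analysis: six behaviours, none leading; Table 1: ten rows |
| Which kind? | Abstract and text: lifestyle and drug adherence | Table 1: also cholesterol, blood pressure, BMI, CVD risk |
| CVD risk primary? | Table 1: yes | Discussion: no |
| Drug adherence? | Abstract, text and Table 1: primary, summarised as a mean | Data analysis: not among the outcomes named |
| Time point? | Sample size: 52 weeks | Data analysis: T2 regressions are additional; overall score has none |
| Scale? | Sample size: a proportion | Third analysis: a standardised score |

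**2. The plan's own figure**

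Per-arm size before clustering: n = [z(alpha)·√(2p̄(1−p̄)) + z(0.80)·√(p1(1−p1)+p2(1−p2))]² / (p1−p2)², with p1 = 0.50, p2 = 0.65, p̄ = 0.575.

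The design effect at 30 patients per practice (600/20) is 1 + 29 × 0.04 = 2.16.

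- Two-sided: 170 × 2.16 = 368 per arm. Power at 300 per arm is 71.7%.
- One-sided: 134 × 2.16 = 290 per arm. Power at 300 per arm is 81.4%.

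The stated 300 per arm is close to the one-sided result and is not reached two-sided. Sidedness is not stated. That is a separate matter. What counts here is that either version spends the whole 0.05 on one comparison.

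**3. False-positive risk with six co-primary behaviours**

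Assume each is tested at 0.05. The Data analysis section gives no per-test level, so this is carried over from the sample size section.

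- Independent tests: 1 − 0.95⁶ = 0.265, about 26%.
- Equal pairwise correlation between test statistics (assumed; simulated, two-sided): 24% at 0.3, 21% at 0.5, 16% at 0.7.

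These figures cover one time point. They also take each test to hold its nominal 5%.

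**4. Would a correction alone be enough?**

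Bonferroni over six gives 0.05/6 = 0.0083 per test. Suppose a single behaviour showed the full 50% against 65%. With an effective 300/2.16 = 138.9 per arm, power would be 45.6% two-sided (55.4% one-sided). Reaching 80% would take 566 (491) per arm. With one primary outcome, alpha stays at 0.05 and no patients are added.

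**The case against.** **Multiplicity belongs in the analysis plan.** A correction procedure may well be there, so a reader should not infer that the trial has no error control at all. The conflicts over outcome and time point are in this article, however, and do not depend on what another document adds.

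**The word additional may mean further models, not lower rank.** That reading is possible. It applies to the regressions only, and CVD risk is clearly analysed at 52 weeks. Even so, the lead comparison and the overall score carry no time point, so the reading does not make 52 weeks primary.

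**CVD risk in Table 1 may be a labelling slip.** Probably so, since the Abstract, the text and the Discussion all point to adherence. It still needs correcting.

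Four stronger inferences are tempting but not supported:

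- *Drug adherence goes unanalysed.* Table 1 gives it a mean. It is only missing from the outcomes that the Data analysis section names.
- *Every mean and proportion in Table 1 is a separate independent test, so the error rate is far higher.* The table lists summaries and does not say that all are confirmatory. A mean and a proportion of the same variable overlap, and CVD risk is calculated from other rows.
- *Because nurse and patient "select one item as the goal for behaviour change", single-behaviour effects must be diluted beyond detection.* The agenda offers five items, one of them medication, and a diet goal can bear on fat, fruit and vegetables. Other components reach every intervention patient. An average over six items would be diluted in the same way.
- *The overall score is the quantity that was powered.* The sample size uses a proportion; the score is something else, and its power is not given.

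**Conclusion.** The point stands and should be settled before outcome data are examined. The article powers one adherence proportion at 52 weeks, names no single primary outcome in its analysis, leaves the rank of 52 weeks unclear, and contradicts itself on whether CVD risk is primary.

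For the six behaviours at one time point, the chance of at least one false positive is about 26% under independence and roughly 16% to 24% under assumed correlations of 0.7 to 0.3, against the 5% used for sizing. These figures rest on an assumed 5% per test and on correlations the article does not give. The contradictions themselves rest on no assumption.

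**What to change.** 1. Name one primary outcome: the overall lifestyle-adherence measure over the six items at 52 weeks, compared by the multilevel model with baseline score.
2. Make it agree with the sample size. Either define it as a proportion, for example by classifying each patient as adherent or not, or keep a score and restate the power for that score.
3. Give fat intake a recommendation cut-off, so that it can enter a measure of recommendations achieved.
4. Make secondary: the 12-week results, the individual behaviours, drug adherence, BMI, blood pressure, cholesterol and CVD risk. Any multiplicity procedure for the behaviours can be left to the analysis plan.
5. Align the Abstract, the Variables and measurements text, Table 1, the Data analysis section and the Discussion.

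The cost is wording and a corrected table, plus a fresh power statement if a score is kept. Claims about single behaviours become secondary. A patient-level classification would match the sample size directly but discards information that a score retains.

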## Methods

### Design

The IMPALA study is a cluster-randomised controlled trial involving 20 general practices and 720 patients in the Netherlands. An independent statistician will perform a central block randomisation. Practices will be randomly allocated, 10 practices to the intervention group and 10 practices to the control group, after stratification into 4 geographical regions. Assessments will be made at the inclusion of the patients in the study, at 12 weeks and at 52 weeks. A flowchart of the study is shown in Figure 1.

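### The first-listed tests of the primary outcomes, and those of the secondary outcomes, are t and chi-square tests that ignore the randomised practices; at the plan's own ICC a nominal 5% test has a true type I error of about 18%

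*Protocol article*

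**What the plan says.** All references are to the Protocol article.

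- **Design.** "The IMPALA study is a cluster-randomised controlled trial involving 20 general practices and 720 patients in the Netherlands". Practices are the unit of allocation: "10 practices to the intervention group and 10 practices to the control group, after stratification into 4 geographical regions".
- **Sample size calculation and feasibility of recruitment.** "The power calculation for clustered data analysis assumes an intra-class correlation coefficient (ICC) of 0.04". The same section cites ICCs of 0.06 and 0.03 from earlier general-practice trials and calls 0.04 the expected maximum. It asks for 600 analysed patients (300 per arm) at 52 weeks, out of 720 recruited (36 per practice).
- **Effect evaluation, Data analysis, primary outcomes.** To assess the difference between arms, changes in each lifestyle item are compared first: "We will use a T test for continuing variables", with a chi-square test for dichotomous ones. A multilevel regression with group allocation and baseline score as predictors follows as the second analysis.
- **Same section, secondary outcomes.** "The secondary outcomes will also be analysed for the differences between the arms, using a T test for continuing variables", again with chi-square for dichotomous ones. A multilevel model is then added as a further intention.
- **Same section, 10-year cardiovascular risk.** A multilevel regression is the only method named.

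**The concern.** A two-sample t test or chi-square test on patients treats everyone within an arm as independent. Here patients share a practice and its nurse, and the practice is what was randomised. If outcomes correlate within practices, the variance of the difference between arms is larger than these tests assume, so their p-values are too small.

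The plan acknowledges the correlation when it sizes the trial and then leaves it out of the first-listed test of the primary outcomes. The stated purpose of that test is to assess the difference between arms, which is inference and not description. At stake is a primary or secondary effect reported as significant only because clustering was ignored. The first and second analyses also treat baseline differently (change scores against covariate adjustment). If they disagree, the reader cannot tell whether clustering or baseline handling is the cause.

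**Working it through.** **Inputs**

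- 20 practices, 10 per arm (Design).
- 600 analysed patients (Sample size calculation), so 600 / 20 = 30 per practice. Recruited size, before any loss: 720 / 20 = 36.
- ICC 0.04; earlier trials 0.03 and 0.06 (Sample size calculation).
- "alpha = 0.05, power = 0.80" (Sample size calculation). Sidedness is not stated; two-sided is assumed.
- ICCs of 0.01 and 0.02 are added as an assumed lower range, because the plan calls 0.04 a maximum.

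**The plan's own figure.** The article gives no error rate for the unadjusted tests, so there is none to reproduce. Its sample size of 300 per arm does not reproduce from its inputs: 170 per arm without clustering, times 2.16, is 367. That is a separate matter; here the 600 serves only to give 30 patients per practice.

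**Step 1: design effect.** DE = 1 + (m - 1) x ICC. For m = 30 and ICC 0.04: 1 + 29 x 0.04 = 2.16.

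**Step 2: true type I error of the unadjusted test.** The test statistic has variance DE instead of 1 under the null hypothesis, so

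type I error = 2 x [1 - Phi(1.96 / sqrt(DE))].

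For DE = 2.16: 1.96 / 1.470 = 1.334, and 2 x [1 - Phi(1.334)] = 0.182.

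**Step 3: range**

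| ICC | DE, m = 30 | Type I error, m = 30 | DE, m = 36 | Type I error, m = 36 |
|---|---|---|---|---|
| 0.01 | 1.29 | 8.4% | 1.35 | 9.2% |
| 0.02 | 1.58 | 11.9% | 1.70 | 13.3% |
| 0.03 | 1.87 | 15.2% | 2.05 | 17.1% |
| 0.04 | 2.16 | 18.2% | 2.40 | 20.6% |
| 0.06 | 2.74 | 23.6% | 3.10 | 26.6% |

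**Step 4: simulation.** 40,000 null trials with 10 practices per arm and ICC 0.04, using a normal outcome for the t tests and a beta-binomial outcome with mean 0.5 for chi-square:

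| Test | m = 30 | m = 36 |
|---|---|---|
| Patient-level t test | 18.1% | 21.0% |
| Chi-square | 18.6% | 20.5% |
| Chi-square, Yates correction | 16.9% | 18.8% |
| t test on practice means, 20 - 2 = 18 df | 4.9% | 5.0% |

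The simulation agrees with the formula, and analysing at practice level restores the nominal rate.

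**The case against.** The strongest reply is that the same section already plans multilevel regression for the primary lifestyle outcomes and the secondary outcomes, and names nothing else for 10-year risk. This stands as a limit on the point. A reader might infer that the trial's inference as a whole ignores clustering; the article does not support that. The fault is narrower: unadjusted tests come first, are offered as the assessment of the difference, and are not subordinated to the multilevel model.

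A second reply is that a condensed article may leave the order of precedence to the full protocol or analysis plan. That answers an omission, but not a test that the article names and that is invalid for its design. It does rule out two further inferences:

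- that the investigators would report whichever p-value is significant, since the rule of precedence may be set elsewhere;
- that the overall adherence score will be analysed without allowing for practices. For that score the article says only "The score of the intervention group will be compared with that of the control group" and names no test, so nothing wrong is stated.

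Third, 18% is conditional. The ICC of 0.04 is the expected maximum, set for self-reported adherence at 52 weeks. The tests compare changes, and the secondary outcomes are attitudes, risk perception and the like; no ICC is given for any of these. This stands, and is why the range starts at 0.01. Inflation remains at every positive ICC shown.

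Finally, a reader might compound 18% over the six lifestyle items into a study-wide error rate. The documents do not support that: the items come from the same patients and are not independent. Even six independent, valid 5% tests would give 1 - 0.95^6 = 26%, so most readings of such a figure would mix multiplicity with clustering. Only the per-test error is claimed here.

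**Conclusion.** The point holds in this limited form. The article names a method that is invalid for a cluster-randomised design as its first assessment of the primary outcomes, and names it again for the secondary outcomes. Under the plan's own ICC of 0.04 and 30 analysed patients per practice, a nominal 5% test has a true type I error of about 18%, or about 21% at 36 per practice. It is 15% and 24% at the cited ICCs of 0.03 and 0.06, and about 8% at 0.01.

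These figures assume a two-sided test, equal practice sizes, no allowance for the regional stratification, and an ICC that carries over to the outcome tested. The multilevel models already planned keep the problem from reaching the whole analysis, but they do not make the first-listed tests valid. The text should be changed before any outcome is analysed.

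**What to change.** 1. Drop the patient-level t and chi-square tests, or state that arm-level summaries are descriptive and carry no p-values.
2. For the primary outcomes, name one analysis on which inference rests. Either use the multilevel model already planned (patients within practices, adjusted for baseline score, logistic for proportions) with a small-sample correction, because there are only 20 practices; or use a t test on practice means with 18 df.
3. Use the same cluster-adjusted method for the secondary outcomes, without giving them confirmatory status, and name it for the overall adherence score as well.

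The cost is a few sentences of analysis text. No extra patients, practices or data are needed, and the multilevel models are already in the plan. Where practices differ, p-values will be larger than those from the unadjusted tests.

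### The six-item overall adherence score is compared between arms with no stated baseline term or multilevel model, unlike the analyses beside it

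*Protocol article*

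**What the plan says.** The Data analysis section of the effect evaluation declines to choose a single primary outcome; instead "the study will examine 6 different lifestyle changes: smoking, physical exercise, fat intake, fruit, vegetables and alcohol". It then sets out several analyses.

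- First, simple between-arm tests of changes in the single behaviours.
- Second, multilevel regressions of the single behaviours, with allocation and the pre-intervention score as independent variables.
- Third, "constructing a simple standardised overall adherence score for the six lifestyle items". It is meant to express "to what extent, on average, patients achieved the behaviour change goals of the national recommendations for a healthy lifestyle". Its analysis is given in one sentence: "The score of the intervention group will be compared with that of the control group".
- Last, the 10-year cardiovascular risk at 52 weeks, in a multilevel regression on allocation and pre-intervention risk.

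The Discussion defends the self-reported outcomes on the ground that the analysis takes pre-intervention scores into account. Timing of measurements places questionnaires at T0, T1 (12 weeks) and T2 (52 weeks).

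In Table 1, fruit and vegetables are reported as "mean sum score; proportion meeting recommendations". Exercise and alcohol also have a proportion meeting recommendations, and smoking has "proportion smoking". Fat intake has only "35 items; [67] Validated questionnaire mean sum score".

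**The concern.** The sample size section powers the trial on one quantity: self-reported adherence to advice on smoking, diet, alcohol and exercise at 52 weeks, 50% against 65%. The overall score is the only planned analysis that combines these behaviours, so it is where a reader will look for the answer to the powered question. It is also the primary-outcome comparison with the least specification.

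Two things are at stake. Many patients will meet some of the recommendations on entry (non-smokers, for example), so part of the follow-up score reflects where patients started. Adjusting for the T0 score removes some of that variation and any chance imbalance between only 10 practices per arm. Also, practices are randomised, so a comparison that ignored practice would understate the standard error.

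A smaller matter is the fat item. The score is defined by achievement of recommendations, but fat is the one item of the six for which Table 1 shows no recommendation-based form.

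**Working it through.** **Plan's own figure.** The plan gives no standard deviation, correlation or detectable difference for this score, so there is nothing to reproduce. The check compares the text of the analyses and then sizes the gain from adjustment under stated assumptions.

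**Text comparison (Data analysis, effect evaluation).**

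| Analysis | Multilevel model named | Baseline value named | Time point named |
|---|---|---|---|
| Single behaviours, second analysis | yes | yes | T2 in additional regressions |
| Overall score, third analysis | no | no | no |
| 10-year risk | yes | yes | 52 weeks |

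**Inputs.** From the sample size section: ICC 0.04 and 600 patients at 52 weeks (300 per arm). From the Design section: 20 practices. Hence m = 600/20 = 30 per practice. Assumed, because the article gives none: the ICC of 0.04 applies to the score, and the correlation r between T0 and T2 scores lies between 0.5 and 0.7, with 0.3 shown as a low case. Whether 600 follows from the plan's power inputs is a separate question; here it only sets m and the arm size.

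**Variance of a practice mean**, in units of the total variance:
- between practices: 0.04
- within practices: 0.96/30 = 0.032
- sum: 0.072, so the between-practice share is 0.04/0.072 = 0.556 and the within-practice share is 0.444.

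**Adjustment for the T0 score.**
- Case A, baseline explains only within-practice variance: SE ratio = √[0.556 + 0.444(1 − r²)].
- Case B, baseline explains both levels equally well: SE ratio = √(1 − r²).

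| r | 1 − r² | Case A SE ratio (cut) | Case B SE ratio (cut) |
|---|---|---|---|
| 0.3 | 0.91 | √0.960 = 0.980 (2%) | 0.954 (5%) |
| 0.5 | 0.75 | √0.889 = 0.943 (6%) | 0.866 (13%) |
| 0.6 | 0.64 | √0.840 = 0.917 (8%) | 0.800 (20%) |
| 0.7 | 0.51 | √0.782 = 0.884 (12%) | 0.714 (29%) |

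**Detectable difference.** The design effect is 1 + 29 × 0.04 = 2.16. With 300 per arm, two-sided 5% and 80% power, the unadjusted detectable difference is (1.960 + 0.842) × √(2 × 2.16/300) = 2.802 × 0.120 = 0.336 SD. Multiplying by the SE ratios for r = 0.5 to 0.7 gives 0.317 to 0.297 SD in case A and 0.291 to 0.240 SD in case B.

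**Clustering.** If the comparison were run as a simple two-sample test, the true standard error would be √2.16 = 1.47 times the one used. A nominal two-sided 5% test would then reject at |z| > 1.96/1.47 = 1.33, a false-positive rate of about 18%. The article does not say that the score will be tested this way; the figure shows only why the model should be named.

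**The case against.** The strongest reply is that this is silence, not a stated unadjusted analysis. The sentence excludes neither a covariate nor a multilevel model, the Discussion points towards baseline adjustment, and covariate lists are often left to an analysis plan that is not shown here. Baseline-adjusted multilevel analyses of adherence already exist item by item. Much of this stands. A reader might infer that the score will be compared at follow-up only, without baseline and without allowance for practice, and the article does not establish that. What remains is that this section does specify model and covariate for the analyses on either side, so the difference is visible in the text. The Discussion's general remark supports the remedy without applying it to this score. The item-by-item models do not estimate a combined adherence effect.

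A reader might also infer that the score cannot be derived because fat has no cut-off in Table 1, or that a cut-off would be chosen after seeing unblinded data. Neither is supported. That column says how each outcome is reported on its own, the Data analysis section names the national recommendations as the yardstick, and a standardised score of the extent of achievement need not use a yes/no cut-off. The article also says nothing about choosing a fat goal after the fact. Nor does it give item weights, so fat's share of the score is unknown.

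Finally, the 13% to 29% range on its own would flatter the gain. With more than half the variance of a practice mean lying between practices, the smaller case A figures must be shown beside it.

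**Conclusion.** The point holds as a weakness of specification with a modest cost in precision. The analysis closest to the powered quantity lacks the baseline covariate and multilevel model that the same section names for its neighbours. Adding the T0 score would cut the standard error by about 6% to 12% if it explains only within-practice variance, and by up to 13% to 29% if it explains between-practice variance equally well. Both ranges rest on assumed correlations of 0.5 to 0.7 and on applying the planning ICC of 0.04 with 30 patients per practice to this score; a weaker correlation gives less. Because practices are randomised, omitting the baseline score costs precision and leaves chance imbalance in place, but does not by itself invalidate the comparison. The fat-intake matter is a minor clarification, with no effect on the result that can be calculated from the article.

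**What to change.** Replace the one-sentence comparison with a full statement: the overall score is computed in the same way from the T0 and T2 questionnaires, and the arms are compared at T2 in the multilevel model already planned, with practice as the cluster and the T0 score as covariate. Add a line naming the national recommendation against which fat intake is scored and how the fat sum score enters the overall score. Keep the continuous fat score as its own outcome.

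The cost is a change of wording. The lifestyle questionnaires are already planned at T0 and T2, and the multilevel software is already named. The only added work is a rule for patients whose T0 score is incomplete. The wording should be fixed before follow-up data are examined.
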